The major objective of this study is to compare the effectiveness of MCT and BA in the treatment of patients with moderate or major depressive disorders in a routine German outpatient setting. As this is the first study that compares MCT and BA, it serves as a pilot trial intended to generate preliminary data for orientation and hypothesis generation. The primary hypothesis is that MCT and BA differ significantly in reducing depressive symptoms (two-sided hypothesis). A two-sided hypothesis was chosen because MCT and BA have never been compared to date and the existing literature does not allow predictions on the directionality of any difference between the two methods. Secondary outcomes address general psychopathology, psychiatric comorbidity, quality of life, psychosocial functioning, and attrition. In addition, we undertake a secondary process evaluation to investigate the moderating and mediating factors in BA and MCT that influence outcome. We will also be conducting a time to event analysis as MCT is often said to be particularly quick in inducing remission.

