### Treatment retention

Treatment dropouts are defined as patients who discontinue treatment before remission but agree to be assessed at the planned assessment time points. Study dropouts are patients who drop out of both treatment and assessment. Patients who withdraw their informed consent to participate in the study are study dropouts but may continue treatment as planned. Patients remitted at the mid-treatment assessment (after 3 months of treatment) can end therapy early and are considered “early successes.” Mid-treatment assessment will then be replaced by post-treatment assessment.

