### Statistical analyses

Hypothesis will be tested by performing analyis on the whole database including all randomized patients (intention-to-treat analysis). Multiple imputation procedure will be used to replace missing data. We will use linear mixed models (LMM) as they have the advantage of using all available data of each subject. LMM analyses also offer the opportunity to choose an appropriate covariance structure reflecting the potential dependence due to repeated measurements (77). Adjustment for baseline measure will be chosen as this increases statistical power and accounts for regression to the mean (78). All continuous outcomes will be analysed as change from baseline with a random intercept for the participant, time as within-groups factor, study group as well as gender as fixed effect and adjustment for baseline measure. The study hypothesis will be tested on the main effect for group. The estimation of effect size will be based on the imputated dataset and Cohen's d will be calculated for continuous data and numbers needed to treat (NNT) for binary data. The appropriate forms of mixed regression will be chosen for categorical outcome variables, counts and in case of non-normal residuals (poisson, gamma, negative binominal, etc.). To identify predictors or moderators related to treatment outcome, mixed regression methods will be used.

Negative effects will be identified by analyzing and reporting the amount of participants that experienced a clinical significant deterioration [according to Jacobson and Truax (79)].For the time to event analysis, onset of remission will be used as the dependent variable and group assignment as the independent variable. Here, remission will be defined as a score of < 6 on the weekly QIDS-SR16 rating. Patients who do not achieve remission within the 6 months of treatment or dropped out will be censored. No missing data will be substituted for this analysis. The *Kaplan-Meier method* will be used to estimate time to remission (in weeks) and remission rates. The main hypothesis will be tested by comparing the estimated remission rates in both groups using the log-rank test. *Cox proportional hazards regression* will be used to calculate the hazard ratios, to evaluate the influence of covariates for the adjusted analyses and to perform the subgroup analyses.

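### The log-rank test on QIDS-SR16 remission is labelled the test of the main hypothesis, a role already held by post-treatment HRSD-24; its censoring of dropouts also needs a sensitivity bound

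*Protocol article*

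**What the plan says.** **Which test carries the main hypothesis.** The Protocol article, Sample size, names HRSD-24 severity at post-treatment as the outcome for the main hypothesis, describes the testing as confirmatory and two-tailed, and derives 64 patients per condition from it. Statistical analyses then tests the study hypothesis on the group effect of the linear mixed model. Later in that section, in the time-to-event paragraph, comes: "The main hypothesis will be tested by comparing the estimated remission rates in both groups using the log-rank test". The Introduction brings this analysis in only as an addition, after the secondary outcomes and the process evaluation: "We will also be conducting a time to event analysis".

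**Event and censoring.** For this analysis "remission will be defined as a score of < 6 on the weekly QIDS-SR16 rating". The censoring rule is: "Patients who do not achieve remission within the 6 months of treatment or dropped out will be censored". Also, "No missing data will be substituted for this analysis". Kaplan-Meier, log-rank and Cox regression are then applied.

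**Who is a dropout.** Treatment retention gives two kinds: "Treatment dropouts are defined as patients who discontinue treatment before remission but agree to be assessed at the planned assessment time points", and "Study dropouts are patients who drop out of both treatment and assessment". Patients who stop at mid-treatment because they have remitted are classed as early successes, not as dropouts.

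**The concern.** The label matters because it decides what the trial may claim. The log-rank comparison uses a different instrument (QIDS-SR16, not HRSD-24), a different source (self-report, not a blinded interviewer) and a different scale (time to an event, not a score), and it has no power calculation. A significant log-rank result beside a null HRSD result could be reported, on the text as printed, as confirming the main hypothesis.

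The censoring rule matters because Kaplan-Meier, log-rank and Cox treat a patient censored in a given week as having the same later chance of remission as those still followed. The article neither states nor justifies that assumption. If patients who leave are mostly those who are not improving, and one arm loses more of them, that arm can appear to remit faster when it does not. The Discussion expects faster symptom reduction with one of the treatments, and attrition is itself a secondary outcome, so a spurious difference in speed would bear on a question the authors mean to answer.

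**Working it through.** **1. The plan's own figure.** Inputs from Sample size: d = 0.5, two-sided 5%, power 80%, 1:1. The exact two-sample t-test needs 63.77 per arm, rounded up to 64, with power 0.801 at 64. The stated 64 per condition reproduces. It belongs to the HRSD comparison; no figure is given for the time-to-event analysis.

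**2. Family-wise error if both tests were main tests at 5%.**
- Independent tests: 1 − 0.95² = 0.0975. Upper bound: 0.05 + 0.05 = 0.10.
- Correlated tests: 1 − P(|Z₁| < 1.96 and |Z₂| < 1.96). With an assumed correlation of 0.5 this is 0.091; with 0.7 it is 0.083.

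Hence about 8% to 10%.

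**3. Effect of censoring, first model.** All rates are assumptions. Remission falls in weeks 4 to 26. Only patients who would never remit drop out, in weeks 2 to 20.
- *Single arm:* true remission 40%, dropout 24%. If all dropouts left at the start, the estimate would be 0.40 / (1 − 0.24) = 0.526. Because they stay in the risk set until they leave, the simulated Kaplan-Meier value is 0.493.
- *Two arms, 64 each, true remission 45% in both.* With 10% v 40% of non-remitters dropping out, overall dropout is 0.55 × 0.10 = 5.5% v 0.55 × 0.40 = 22%, and Kaplan-Meier reads 47% v 55%. With 10% v 50% it reads 47% v 58%.

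| Non-remitters who drop out | Log-rank rejection (nominal 5%) |
|---|---|
| 10% v 10% | 4.8% |
| 10% v 20% | 6.0% |
| 20% v 30% | 6.1% |
| 10% v 30% | 7.3% |
| 10% v 40% | 11.0% |
| 10% v 50% | 16.7% |

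Each row rests on 4,000 simulated trials, so the standard error is about √(0.06 × 0.94 / 4000) = 0.4 points at 6% and √(0.167 × 0.833 / 4000) = 0.6 points at 16.7%.

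**4. Second, milder model.** Over 24 weeks, half the patients are improvers (85% remit) and half non-improvers (15% remit), the same in both arms. Only non-improvers drop out, 10% of them in the comparator arm. With 40%, 60% or 80% leaving the other arm, the spurious hazard ratio is 1.08, 1.16 or 1.31 and rejection is 6.4%, 9.9% or 19.1%. The last figure needs an eight-fold gap.

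**5. Controls (second model).**
- Dropout unrelated to prognosis, 40% v 10%: hazard ratio 1.00, rejection 4.1%.
- Informative but equal dropout, 60% of non-improvers in both arms: both Kaplan-Meier rates rise from 50% to about 58%, but the hazard ratio is about 1.01.

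Overstated remission therefore needs a poorer outlook among dropouts; a biased comparison needs unequal dropout as well.

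**6. The alternative, dropouts kept as not remitted.** When dropout is unrelated to prognosis, this analysis is the biased one. In the first model's setting, with overall dropout probabilities of 5% v 25%, 10% v 30% and 10% v 40%, it rejects in 9.8%, 10.8% and 15.1% of trials; the planned log-rank rejects in 5.6%, 4.9% and 4.7%. In the second model, 40% v 10% dropout gives a hazard ratio of 0.84. In the three informative scenarios of step 4 it gives 0.93 to 0.97, slightly against the arm with more dropout.

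**The case against.** **On the label.** The Introduction, Sample size, Primary outcome measure and Discussion all place the primary hypothesis on depressive severity. The disputed sentence sits in the time-to-event paragraph and may simply mean the main comparison of that analysis. The Introduction also calls the trial a pilot for generating hypotheses. This is fair as a guess at intent, and the 8% to 10% applies only if both tests are read as main tests. But Sample size uses the same term for the HRSD outcome and calls that test confirmatory, so the printed wording is a contradiction.

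**On the censoring.** A reader might infer from "Treatment dropouts are defined as patients who discontinue treatment before remission" that censoring is informative by definition. The document does not support that. Every censored patient in any Kaplan-Meier analysis is event-free. The phrase covers treatment dropouts only, not study dropouts. Remission under Primary outcome measure is HRSD ≤ 8, whereas the event here is QIDS-SR16 < 6, so a dropout may already have had the event. Nothing in the article says that dropouts do worse or that attrition will differ between two programmes built to be structurally alike. The larger error rates need a four- to five-fold gap in dropout among non-remitters, and the first model assumes that no dropout would ever have remitted. All of this stands, and it makes the second point conditional.

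**On sensitivity analyses.** An unseen analysis plan may contain them. Their absence from an article is not counted as a fault; the recommendation concerns how the stated analysis should be reported.

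**Conclusion.** The contradiction over the main hypothesis is certain from the text and should be corrected. Its size is a family-wise error of about 8% to 10%, conditional on both tests being used as main tests at 5%.

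The censoring point holds only conditionally. Kaplan-Meier remission is overstated if dropouts have a poorer outlook, and the arm comparison is biased if dropout also differs between arms. With equal true remission, the first model's unequal-dropout scenarios give about 6% to 17% rejection instead of 5%, near the lower end for moderate gaps. These are assumed scenarios, not estimates for this trial.

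Two stronger readings are not supported. One is that the planned log-rank analysis is wrong and should give way to a competing-event analysis: with unequal dropout unrelated to prognosis, the planned test keeps its level and the replacement does not. The other is that early successes will be censored when nearly remitted: the article does not say that weekly ratings stop with therapy, or how these patients enter this analysis. The HRSD mixed model is unaffected by the censoring rule.

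**What to change.** 1. In the time-to-event paragraph of Statistical analyses, replace *The main hypothesis* by *The secondary hypothesis on time to remission*. The HRSD-24 contrast at post-treatment is then the only confirmatory test. This is a wording change and costs nothing.
2. Keep the planned Kaplan-Meier, log-rank and Cox analysis with dropouts censored. Beside it, report as a sensitivity bound the cumulative incidence of remission by arm with dropouts kept as not remitted to the end of the treatment period, together with the dropout numbers per arm. If the two analyses agree, the conclusion on speed of remission is less exposed to the dropout assumption; if they differ, say so and do not claim a difference in speed.

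The cost is one extra analysis on data already collected. The downside is that the bound penalises the arm with more dropout when dropout is unrelated to prognosis, and counts as failures any dropouts who remit later. It should therefore stand beside the planned analysis and not replace it.

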### Eligibility criteria

Patients aged 18 or above will be included if they (1) have a main diagnosis of a depressive episode [as diagnosed by the Structural Clinical Interview for DSM-IV (SCID I)] (2) have a depression severity score of 16 or higher measured by the 24-item Hamilton Rating Scale for Depression (HRSD-24) (3) have read and signed an informed consent form, (4) are able and willing to participate reliably in therapy and assessment procedures. Exclusion criteria are (1) lifetime diagnosis of a psychotic or bipolar disorder, (2) intellectual deficits (IQ < 85), (3) acute suicidality, (4) a main diagnosis other than MDD that requires prioritized treatment and (5) acute substance dependency (according to DSM-5) that requires detoxification treatment. Participation is possible after completion of detoxification treatment and a 2 month period of abstinence.

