### Randomization

After completion of the baseline assessment, participants are randomised equally (1:1) to the two groups (MCT or BA). Randomisation is stratified by gender to avoid biases due to unbalanced gender distribution. Randomization will be conducted by using the program BiaS (11.02) (50). The allocation is concealed from participants and researchers. After randomization, participants are informed about the start date of the treatment. In the first treatment session participants will be informed about which condition and therapist they are assigned to.

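### The deciding test for time to remission is valid, but it uses neither baseline severity nor the randomisation stratum and so gives up a modest, assumption-dependent amount of power

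*Protocol article*

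**What the plan says.** All of the following is in the protocol article.

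- **Event and comparison (Statistical analyses).** In the time-to-event analysis, "remission will be defined as a score of < 6 on the weekly QIDS-SR16 rating". In the same paragraph, "onset of remission will be used as the dependent variable and group assignment as the independent variable". Patients without remission by 6 months and dropouts are censored.
- **Deciding test (Statistical analyses).** "The main hypothesis will be tested by comparing the estimated remission rates in both groups using the log-rank test". No strata or covariates are attached to it.
- **Role of the Cox model (Statistical analyses).** It supplies hazard ratios and is used "to evaluate the influence of covariates for the adjusted analyses and to perform the subgroup analyses". The covariates are not listed, and the Cox model is not the named test.
- **Continuous outcomes (Statistical analyses).** "Adjustment for baseline measure will be chosen as this increases statistical power and accounts for regression to the mean". The mixed model has "study group as well as gender as fixed effect and adjustment for baseline measure".
- **Design (Randomization).** "Randomisation is stratified by gender to avoid biases due to unbalanced gender distribution". Patients learn their condition in the first treatment session.
- **Data available (Assessments, Table 2).** HRSD and QIDS-C16 are taken at baseline and again at pre-treatment. The self-rated QIDS-SR16, on which the event is defined, is not in Table 2. It appears under Process parameters as a weekly measure.

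**The concern.** The section gives a reason for adjusting continuous outcomes, namely power, and applies it to baseline and gender. It does not carry that reason over to the test of time to remission. The case for doing so is at least as good here, because the event is an absolute threshold. A patient who starts at a higher score has further to fall, so starting severity plausibly predicts when the threshold is reached. When a prognostic variable is left out, the marginal hazard ratio behind the log-rank test is pulled towards 1 and some power is lost.

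Speed of remission is a stated question of the trial: the Introduction announces the analysis, and the Discussion expects faster improvement with MCT. The sample size was set for the HRSD-24 comparison only. If the speed test is short of events, power that could be recovered from data already collected is worth having.

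**Working it through.** **1. The plan's own figure.** Inputs (Sample size): d = 0.5, two-sided 5%, power 80%.

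Normal approximation: n per arm = 2(1.960 + 0.842)²/d² = 2 × 7.849/0.25 = 62.8, so 63. The exact t-test gives 63.77, so 64, with power 80.1%. The stated 64 per arm (128 in total) reproduces. It concerns HRSD-24 only; no figure is given for time to remission.

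**2. Information for the log-rank test.** Schoenfeld's formula: events for 80% power = 4 × 7.849/(ln HR)² = 31.40/(ln HR)². Power with D events = Φ(√D × ln HR/2 − 1.96).

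Assumption: 51 to 64 events, i.e. 40% to 50% of 128. The Introduction says about half of CBT patients remit, but gives no rate for this population. Example, HR 1.5 and 64 events: 8 × 0.4055/2 − 1.96 = −0.34, so 37%.

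| HR | events for 80% power | power with 51 to 64 events |
|---|---|---|
| 1.5 | 191 | 30% to 37% |
| 1.75 | 101 | 52% to 61% |
| 2.0 | 66 | 70% to 79% |

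**3. Unadjusted log-rank against adjusted Cox, by simulation.** From the article: 64 per arm, 1:1 allocation stratified by gender. Assumed: exponential remission times over 26 weeks, control remission 35% or 50%, 15% dropout, 60% in one gender category, gender log hazard ratio 0.2 (0 in the first column below), and baseline severity with log hazard ratio 0, 0.3, 0.5 or 0.8 per SD (hazard ratios 1, 1.35, 1.65, 2.2). There were 1,500 runs per scenario. Each cell shows power (%) of the unadjusted log-rank → Cox adjusted for severity and gender.

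| HR, control remission | 0 | 0.3 | 0.5 | 0.8 |
|---|---|---|---|---|
| 1.5, 35% | 29.7 → 29.0 | 27.5 → 27.9 | 25.5 → 26.8 | 23.4 → 28.1 |
| 1.5, 50% | 37.1 → 36.9 | 38.1 → 40.7 | 34.6 → 39.5 | 28.1 → 39.6 |
| 1.75, 35% | 54.1 → 52.8 | 50.4 → 51.3 | 48.9 → 52.0 | 38.5 → 47.4 |
| 1.75, 50% | 65.3 → 65.3 | 61.7 → 64.5 | 54.7 → 62.9 | 48.5 → 62.9 |
| 2.0, 35% | 70.2 → 70.3 | 68.8 → 70.4 | 66.6 → 70.7 | 57.1 → 70.5 |
| 2.0, 50% | 84.9 → 84.7 | 82.1 → 84.9 | 78.1 → 84.9 | 68.3 → 83.6 |

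Gains in points: −1.3 to +0.1 with no prognostic effect, 0.4 to 2.8 at 0.3, 1.3 to 8.2 at 0.5, and 4.7 to 15.3 at 0.8. Stratifying the log-rank by gender alone moved power by less than 1 point throughout. Under the null, all tests ran at 4.1% to 5.7%. The Monte Carlo standard error is about 1.3 points per power figure. Weekly ties were not modelled.

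**4. The test proposed below.** A covariate-adjusted log-rank test stratified by gender (128 patients, about 50 to 64 events) kept its size near 5% and cost nothing when severity was not prognostic. It gained about 1, 4 and 9 points at log hazard ratios of 0.3, 0.5 and 0.7 per SD.

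**5. Without proportional hazards.** Linear symptom trajectories were simulated with a baseline-to-week-24 correlation of 0.3 or 0.5. The adjusted Cox Wald test with model-based variance ran at 6% to 8% type I error. After size correction, log-rank against Cox was 65% against 64% and 62% against 65%. With robust variance, a rough run gave 5.4% type I error and gains of about 3 and 11 points. The covariate-adjusted log-rank test gained 6 to 9 points under linear trajectories.

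**The case against.** The strongest reply is that nothing here is an error. A log-rank test between randomised arms is standard and valid, and it held its size in the simulations. The adjusted Cox analysis is already planned, so only the ranking of two planned analyses is in dispute. That stands. A reader might infer that the plan throws away baseline information for this endpoint, or leaves chance imbalance in severity wholly uncorrected. The planned Cox analyses rule out both readings.

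Other parts of the objection also stand:

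- **Gender.** Its contribution to power is negligible. Including it aligns the analysis with the design and little more.
- **The parallel with continuous outcomes is imperfect.** Those are adjusted for their own baseline measure. Here the event scale is self-rated and not listed at baseline, so the covariate must be a clinician-rated proxy. The entry threshold of HRSD-24 of at least 16 narrows the range of severity further.
- **Size.** The gain depends on one unknown, the prognostic strength of severity. A 21-point gain can be produced (55% to 76%), but only by assuming a hazard ratio of 2.7 per SD, and it should not be relied on.
- **Estimand.** An adjusted Cox test moves the target from a marginal to a conditional hazard ratio and leans on proportional hazards. Statisticians differ on that trade.

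The last item is met by a covariate-adjusted log-rank test, which keeps the marginal comparison. What remains is that the article does more than stay silent: it names the deciding test and gives group as its independent variable. A more precise adjusted result therefore could not settle the question.

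**Conclusion.** The point holds as a minor efficiency improvement to a secondary analysis. The deciding test for time to remission names no strata or covariates, although severity is collected, randomisation is stratified by gender, and the plan's own argument for adjustment applies.

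The gain cannot be derived from the article. Under assumed links between severity and remission it is about 0 to 3 points of power if the link is weak and roughly 4 to 9 points if moderate. With a small hazard ratio and few events, a moderate link may give as little as 1 point. Nearly all of the gain comes from severity. It would not rescue the endpoint: at HR 1.5 with 51 to 64 events, the starting power is only 30% to 37%.

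Because the quoted sentence speaks of a main hypothesis, a reader might infer that the trial's primary conclusion rests on this log-rank test. The article does not support that. The primary outcome is HRSD-24 severity at post-treatment, and the study hypothesis is tested on the group effect in the mixed model. That test and its sample size are unaffected.

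**What to change.** In Statistical analyses, replace the log-rank sentence with wording such as:

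> Time to remission will be tested with a covariate-adjusted log-rank test, stratified by gender and adjusted for pre-treatment QIDS-C16 (baseline value if missing). The hazard ratio will come from a Cox model stratified by gender and adjusted for the same covariate, with robust variance. Kaplan-Meier curves and the unadjusted log-rank test are supportive.

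The covariate-adjusted log-rank test and the adjusted Cox test are different tests, so the text should say which one decides. The covariate should be a rating taken before the first treatment session, when patients learn their condition.

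The cost is slightly more analysis work, with no new data and no extra patients. The Cox hazard ratio becomes conditional on severity. QIDS-C16 is a clinician-rated stand-in for the self-rated event scale, so its prognostic strength is assumed; if it has none, the proposed test lost nothing in simulation. The change should be fixed before outcome data are analysed.

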### Sample size

The primary outcome measure to test the main hypothesis is the severity of depressive symptoms at post-treatment, assessed by the Hamilton Rating Scale for Depression [HRSD, 24-items version (47)]. Confirmatory two-tailed testing of two conditions requires a sample size of *n* = 64 patients in each condition (total *N* = 128 patients). The sample size calculation (48) is based on a power of 80% and a type I error of 5%, as well as an effect size of *d* = 0.5. The estimated between subjects effect size is set according to the one defined by the National Institute of Clinical Excellence (49) for clinical significant difference (*d* ~ 0.5).

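### The Statistical analyses section gives the name of the main hypothesis, already tied to post-treatment HRSD-24, to a log-rank test on self-rated remission

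*Protocol article*

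**What the plan says.** The Sample size section of the Protocol article defines the term: "The primary outcome measure to test the main hypothesis is the severity of depressive symptoms at post-treatment", measured with the 24-item HRSD. It continues with "Confirmatory two-tailed testing of two conditions requires a sample size of" 64 patients per condition, and gives 80% power, a 5% type I error and "as well as an effect size of *d* = 0.5".

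The Statistical analyses section describes a linear mixed model for change from baseline and says of it: "The study hypothesis will be tested on the main effect for group". Its second paragraph turns to the time-to-event analysis, defines remission as a weekly QIDS-SR16 score below 6, and states: "The main hypothesis will be tested by comparing the estimated remission rates in both groups using the log-rank test". It gives no order between the two tests, and no significance level for the log-rank test.

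Other sections bear on the status of the two tests:

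- The abstract and the Primary outcome measure section name the HRSD as primary.
- The last paragraph of the Introduction states the primary hypothesis as a difference in reducing depressive symptoms. It then brings in the time-to-event analysis as something done in addition.
- The Process parameters section lists the QIDS-SR16 as a process measure.
- The Introduction also says of the trial that "it serves as a pilot trial intended to generate preliminary data for orientation and hypothesis generation".

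**The concern.** One term, the main hypothesis, is attached to two tests that can disagree. They differ in instrument, rater, endpoint and handling of missing data. The HRSD is rated by blinded interviewers. The QIDS-SR16 is filled in by patients who learn their condition at the first treatment session.

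The Discussion concedes that the between-group difference may be too small to reach significance, and separately expects MCT to act faster. In that setting, a second test that the plan itself calls the test of the main hypothesis could be put forward when the HRSD-24 result is null. The 5% error rate and the sample size were set for the HRSD-24 comparison alone.

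**Working it through.** **1. The plan's own figure.** Inputs from the Sample size section: d = 0.5, two-sided α = 0.05, power 0.80. Allocation is 1:1 (Randomization section).

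Normal approximation: n per arm = 2(1.960 + 0.842)² / 0.5² = 2 × 7.85 / 0.25 = 62.8, so 63. With the noncentral t distribution, power is 79.5% at 63 per arm and 80.1% at 64. The stated 64 per arm is therefore reproduced, for one comparison of means at two-sided 5%. Nothing in it provides for a second test.

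**2. The two tests side by side.**

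| | Mixed model | Log-rank |
|---|---|---|
| Label in Statistical analyses | study hypothesis | main hypothesis |
| Label in Sample size | main hypothesis (HRSD-24) | not mentioned |
| Measure | HRSD-24 | QIDS-SR16 below 6 |
| Rater | blinded interviewer | patient, weekly |
| Quantity | change in severity | time to a threshold |
| Missing data | multiple imputation | none substituted; dropouts censored |
| α stated | 5% (Sample size) | none |

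**3. Error rate if either result could carry the claim.** Two assumptions are needed, and neither is in the article: that success is claimed when at least one test is significant, and that the log-rank test is also run at two-sided 5%.

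Independent tests: 1 − (1 − 0.05)² = 1 − 0.9025 = 9.75%. Upper bound under any dependence: 0.05 + 0.05 = 10%.

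Correlated tests: 1 − P(|Z₁| ≤ 1.96 and |Z₂| ≤ 1.96) for a bivariate normal with correlation ρ. The article gives no ρ, so a range is shown:

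| ρ | Error rate |
|---|---|
| 0 | 9.75% |
| 0.3 | 9.5% |
| 0.5 | 9.1% |
| 0.7 | 8.4% |
| 0.8 | 7.8% |
| 0.9 | 7.0% |
| 1 | 5% |

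**4. The two ways to close the gap.** With the HRSD-24 test alone confirmatory, the error rate is 5% and power at 64 per arm stays at 80.1%. With both tests confirmatory at 0.025 each, the familywise rate is at most 5%, but HRSD-24 power at 64 per arm falls to 71.2%, and 78 per arm would be needed for 80%.

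**5. The HRSD-24 parameter.** The Sample size section sets the comparison at post-treatment. The Statistical analyses section tests a group main effect in a model with time as a within-subject factor. If more than one visit after baseline enters that model, the main effect is a difference averaged over those visits. It then need not equal the post-treatment difference to which d = 0.5 refers.

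**The case against.** The strongest reply is that the log-rank sentence is local. Its paragraph announces the time-to-event analysis, restricts the remission definition and the missing-data rule to that analysis, and goes on to adjusted and subgroup Cox models. In that setting the main hypothesis can mean the main, unadjusted comparison within the time-to-event analysis. The rest of the article supports this: the abstract, the Introduction, the Sample size section and the Primary outcome measure section all point to depression severity, with the HRSD as the measure wherever one is named.

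Much of this stands. A reader might infer that the plan fixes no single confirmatory outcome. The article does not support that, because the primary outcome is named consistently and only one comparison is sized. A reader might also infer that the trial's false positive rate is 8–10%. That does not follow either. No section says that a positive result on either test suffices, no level is given for the log-rank test, and 8–10% holds only for correlations up to about 0.77. Both tests concern depression in the same patients, so a higher correlation cannot be ruled out.

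The benign reading still has to be supplied by the reader. The sentence carries no such restriction, and the Sample size section has already given the term another meaning.

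The tension between a confirmatory test and a hypothesis-generating pilot does not change which outcome is primary. How the investigators describe the trial's purpose is for them to decide.

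**Conclusion.** The concern holds as a contradiction in labelling. The main hypothesis is HRSD-24 severity at post-treatment in one section and time to QIDS-SR16 remission in another, and only the first is sized. The consequence is conditional: if either result were reported as confirming the main hypothesis, with each test at 5%, the false positive rate would be between 5% and about 10%, depending on an unknown correlation. It is 5% if the HRSD-24 test is the only confirmatory one, which is what the rest of the article implies.

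A related mismatch needs settling at the same time: the quantity that was sized and the quantity that the mixed model tests are described differently.

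**What to change.** 1. Replace the log-rank sentence in Statistical analyses with wording such as: *Speed of remission is a secondary hypothesis; a log-rank test will compare the time-to-remission curves of MCT and BA.* This also says more exactly what the test compares, since a log-rank test contrasts whole curves rather than remission rates.
2. State in the same section that the HRSD-24 group comparison is the only confirmatory test, at two-sided 5%.
3. Reconcile Sample size with Statistical analyses, so that the confirmatory HRSD-24 parameter is the one for which 64 per arm was calculated.

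Items 1 and 2 are changes of wording. Sample size, data collection and conduct stay as they are, and the log-rank result gives up any confirmatory status. Item 3 may be more than wording: if the group main effect averages over several visits, choosing the post-treatment contrast changes the tested parameter, and keeping the main effect means restating what the sample size calculation refers to.
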